# Treatment of Hyperlactatemia in Acute Circulatory Failure Based on CO_2_-O_2_-Derived Indices: Study Protocol for a Prospective, Multicentric, Single, Blind, Randomized, Superiority Study (The LACTEL Study)

**DOI:** 10.3389/fcvm.2022.898406

**Published:** 2022-06-23

**Keywords:** acute circulatory failure, hyperlactatemia, pCO_2_ gap, resuscitation, anaerobic metabolism, sepsis, cardiac surgery shock, lactic acidosis

## Abstract

**Background:**

Hyperlactatemia is a biological marker of tissue hypoperfusion with well-known diagnostic, prognostic, and therapeutic implications in shock states. In daily clinical practice, it is difficult to find out the exact mechanism underlying hyperlactatemia. Central venous to arterial CO_2_ difference (pCO_2_ gap) is a better parameter of tissue hypoperfusion than the usual ones (clinical examination and mixed venous saturation). Furthermore, the ratio between the pCO_2_ gap and p(v–a)CO_2_/C(a–v)O_2_ may be a promising indicator of anaerobic metabolism, allowing for the identification of different causes of tissue hypoxia and hyperlactatemia. The main aim of the study is to demonstrate that initial hemodynamic resuscitation based on an algorithm integrating the pCO_2_ gap and p(v–a)CO_2_/C(a–v)O_2_ ratio vs. usual clinical practice in acute circulatory failure improves lactate clearance.

**Methods:**

LACTEL is a randomized, prospective, multicentric, controlled study. It compares the treatment of hyperlactatemia using an algorithm based on the pCO_2_ gap and P(v–a)CO_2_/C(a–v)O_2_ ratio vs. usual clinical practice in acute circulatory failure. A total of 90 patients were enrolled in each treatment group. The primary endpoint is the number of patients with a lactate clearance of more than 10% 2 h after inclusion. Lactate levels were monitored during the first 48 h of treatment as hemodynamic parameters, biological markers of organ failure, and 28-day mortality.

**Discussion:**

pCO_2_ derivate indices may be of better interest than routine clinical indices to differentiate causes of hyperlactatemia and diagnose anaerobiosis. LACTEL results will provide clinical insights into the role of these indices in the early hemodynamic management of acute circulatory failure in the ICU.

**Clinical Trial Registration:**

www.clinicaltrials.gov; identifier: NCT05032521.

## Introduction

Acute circulatory failure (i.e., shock) is a very common life-threatening condition among patients admitted to intensive care units (ICUs) (1). Historically, treatment of shock has been based on physical examination (skin mottling, capillary refill time, and urine output) and biological macrohemodynamic parameters (blood pressure, arterial lactate, and mixed venous saturation).

During acute circulatory failure, hyperlactatemia remains a parameter widely used to assess tissue hypoperfusion despite its limitations (2). Hyperlactatemia and the clearance of arterial lactate have been demonstrated to be associated with morbidity and mortality in patients with shock and even during/following surgery (3–6). From a physiological perspective, hyperlactatemia can be the result of increased production (type A), reduced elimination (type B), or both (6, 7). Although identification of the exact cause underlying hyperlactatemia is very important for targeted therapy (fluid resuscitation, inotropic or vasopressor support), in clinical practice, it is very difficult to accurately identify the cause of hyperlactatemia (6).

From work carried out over the last 20 years, the pCO_2_ gap has been increasingly recognized as a reliable tool to evaluate tissue perfusion, because it was suggested as a marker of the relationship between cardiac output (CO) and global metabolic demand (8–11). Later, several studies have evaluated the P(v–a)CO_2_/C(a–v)O_2_ ratio as a parameter that was able to provide additional information about anaerobic metabolism in order to identify the causes of hyperlactatemia and to define shock severity (12–14). Based on these studies, authors have proposed different algorithms based on CO_2_-O_2_-derived indices to treat shock and arterial hyperlactatemia (7, 9).

Our hypothesis is that treatment of hyperlactatemia based on CO_2_-O_2_-derived indices would allow for a faster and higher lactate clearance, thus reducing inappropriate therapy and improving outcomes.

## Materials and Methods

### Study Design

LACTEL (*Traitement de l'hyperLACtaTEmie du patient en insuffisance circuLatoire aigue basée sur l'analyse des indices dérivés du CO2: étude randomisée prospective de supériorité*) is a randomized, prospective, multicentric, single-blind, parallel-group, superiority study. It compares the treatment of hyperlactatemia using an algorithm based on the pCO_2_ gap and the pCO_2_ gap/P(a-v)O_2_ ratio vs. usual clinical practice in patients with shock. The study was approved by an independent ethics committee (*Comité de Protection des Personnes Sud Ouest et Outre-Mer* on 8 July 2021, 2021-A101451-40) and was registered (ClinicalTrials.gov: NCT05032521). The study is conducted in ICUs of the University-affiliated tertiary Hospital of Dijon and the University-affiliated tertiary Hospital of Besancon, France. All the patients or their next of kin received written information about the study and gave consent to participate. The design of the study respects the requirements of the Medical Research Involving Human Subjects Act and the Declaration of Helsinki.

Standard protocol items: the study follows the SPIRIT Recommendations for Interventional Trials, and the SPIRIT protocol chronology is presented in Table 1.

**Table 1 T1:** Protocol timeline.

	**ICU admission**	**Enrolment**	**Follow-up**				**End of study**
	**H0 (Day 0)**	**H0 (Day 0)**	**H2**	**H12 (Day 0)**	**H24 (Day 1)**	**H48 (Day 2)**	**Day 28**
Enrolment validation	X						
Randomization		X					
Clinical examination	X	X	X	X	X	X	X
Standard analysis set	X	X	X	X	X	X	
Study analysis set	X	X	X	X	X	X	
Clinical and biological data		X	X	X	X	X	X
Hemodynamic monitoring		X	X	X	X	X	
SOFA score		X	X	X	X	X	X

*ICU, intensive care unit; H, hours at or after enrollment; D, day*.

The first patient was included in December 2021, and the last follow-up was planned until October 2024.

### Study Population

Adult patients are considered for enrollment if they have acute circulatory failure and arterial blood lactate levels ≥3 mmol L^−1^. Acute circulatory failure was defined as systolic blood pressure < 90 mmHg, and/or mean blood pressure <65 mmHg, need for infusion of vasopressor catecholamines, and/or skin mottling, and/or diuresis <0.5 ml kg^−1^ h^−1^ (1, 15). All types of shock will be included: septic, cardiogenic, hemorrhagic, and post-operative.

The inclusion, non-inclusion, and exclusion criteria are provided in Table 2.

**Table 2 T2:** Inclusion, non-inclusion, and exclusion criteria of the study.

**Inclusion criteria**	**Non-inclusion criteria**
• Age ≥ 18 years	• Age <18 years
• Patient or family agreement	• Pregnant or breastfeeding patient
• Arterial blood lactate levels ≥ 3 mmol l^−1^	• No medical insurance
• Acute circulatory failure	• Patient under court order
	• Patient under legal protection • ECMO or Impella support
	**Exclusion criteria**
	• <48 h ICU Lenght of stay

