### Study Intervention

Care of the patients is standardized and follows international guidelines and in-hospital protocols (1, 16–19). Preload dependence is assessed using the passive leg raising maneuver and/or the fluid challenge maneuver. Preload dependence is treated with a fluid bolus (250–500 ml) of Ringer Lactate for over 15 min. Cardiac output is optimized first by optimizing preload, and in the absence of preload dependency, by intravenous administration of dobutamine to obtain a cardiac index (CI) >2.5 L min^−1^ m^−2^. Cardiogenic failure is treated by intravenous administration of dobutamine (2.5–10 μg kg^−1^ min^−1^). Cardiac output can be measured by using echocardiography (Affinity or Epiq Philips™), pulmonary artery catheter, trans-pulmonary thermodilution (PiCCO device, Maquet™), or by Pressure Recording Analytical Method (Mostcare, Vygon™, France) (15). Vasoplegic syndrome is treated by intravenous infusion of norepinephrine (0.01 to 2 μg kg^−1^ min^−1^). Additional use of vasopressin if the norepinephrine dose is over 0.2 μg kg^−1^ min^−1^ is permitted. In accordance with the guidelines, we use a threshold of Hb <70 g/L for transfusion, in the absence of coronary artery disease. In patients with coronary artery disease, the threshold for transfusion is Hb <100 g/L. The mechanical ventilation parameters are adjusted on the basis of arterial blood analysis results. Baseline ventilator settings are as follows: respiratory rate of 10–18 breaths/min, tidal volume of 4–8 ml/kg, positive end-expiratory pressure of 5–10 cmH_2_O, a fraction of inspired oxygen of 0.25–1, targeting proper PaO_2_ of 100–120 mmHg, and PaCO_2_ of 35–45 mmHg. None of the non-hemodynamic therapies will be discontinued, and the drug dose regimen will not be modified. These therapeutic strategies do not differ in the two study groups. In the algorithm group, pCO_2_ is measured by central blood gas analysis.

The study intervention consists of treatment of hyperlactatemia following either an algorithm based on the pCO_2_ gap/P(a–v)O_2_ ratio and pCO_2_ gap or usual clinical practice based on macrohemodynamics, respecting randomization. If hemodynamic deterioration occurs despite hemodynamic optimization, a patient is excluded from the study and is treated following usual clinical protocols.

The algorithm is shown in Figure 1. Usual clinical practice is shown in Figure 2.

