### Randomization

The 1:1 ratio randomization (stratified on center and type of shock) is performed by the investigator after the patient's enrollment, using a dedicated e-platform made with CleanWebTM. The security of this process is assured by individual usernames and newly created passwords for each enrolment. A second check for the inclusion, non-inclusion, and exclusion criteria is required before continuing with the randomization. Technical support is provided by the Research Methodology Support Unit from our university-affiliated hospital, which also keeps a record of the full randomization process. Statistical analysis is performed by a statistician of the Research Methodology Support Unit who is not involved in the study process.

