### Endpoints

The primary endpoint is the number of patients with a lactate clearance over 10% between H0 and H2.

The secondary endpoints are as follows: (1) blood lactate levels at H12, H24, and H48; (2) lactate clearance at H12, H24, and H48; (3) relationship between pCO_2_ gap and blood lactate levels at H2, H12, and H24; (4) relationship between p(v–a)CO_2_/C(a–v)O_2_ and lactate clearance at H2, H12, and H24; (5) relationship between P(v–a)CO_2_ /C(a–v)O_2_ and VO_2_ at H2, H12, and H24; (6) SOFA score on days 0, 1, 2, 7, and 28; and (7) ICU length of stay, hospital length of stay, and 28-day mortality. Patients' follow-up is 28 days after enrolment.

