### Data Collection

Data are collected and recorded on eCRF by a physician who is not involved in the care of the patient, and who is blind to the study groups. All patient-related data are anonymously and numerically coded. Data collection encompasses the following: (1) the demographic characteristics of the population (age, sex, weight, SOFA score, SAPS II score, hospital and ICU admission reason, past medical history, and comorbidities), (2) the pharmacological treatment (type and infusion rate of sedation drugs, maximal dose and duration of norepinephrine and dobutamine, amount of fluid, fluid balance, and amount of blood transfusion), (3) the respiratory parameters (tidal volume, respiratory rate, positive end-expiratory pressure, inspiratory O_2_ fraction, end-tidal CO_2_, and plateau and peak pressure), (4) the hemodynamic state (heart rate, arterial blood pressure, pulse pressure, hourly urinary output, cardiac output, respiratory variation of pulse pressure, and/or stroke volume), and (5) the biological marker (hemoglobin, arterial and mixed venous oxygen saturation, partial pressure of CO_2_ in arterial and venous blood, blood lactate level, bicarbonate, base excess, creatinine, sodium, potassium, and chloride).

The study may be discontinued for an individual patient if the patient (or the person designated by the patient) so desires or if decided by the investigator. Every effort will be made to comply with the study protocol. However, the clinician in charge of the patient may deviate from these instructions at any time if he/she considers it necessary. He/she must note this decision and the reason for it in the case report form. If the study is discontinued, no provision is made for patient replacement. Likewise, patients who discontinued the study for whatever reason will receive standard care for the disease in question.

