## Statistics

### Sample Size Calculation

Based on actual literature, lactate clearance over 10% over a 2-h period is between 50 and 60%. Assuming our hypothesis that an algorithm based on CO_2_-O_2_-derived indices can reach a 2-h lactate clearance over 80%, 82 patients should be randomized in each treatment group with a bilateral alpha risk of 5% and a power of 80%. After taking into account the risk of missing data and patients lost to follow-up (10% of incomplete data), we fixed the sample size to 180 patients, with 90 in each treatment arm.

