### Data Analysis Plan

Normality will be checked graphically with histograms and QQ plots and by the Shapiro-Wilk normality test. Continuous variables will be described as mean ± SD or as median (25–75%, IQR) as appropriate, and categorical variables will be described using a frequency table with a 95% confidence interval for the proportion. The data will be analyzed by intention to treat and per protocol. The two groups will be presented comparatively after randomization. Evaluation of the primary endpoint will be performed by Fisher's exact test. Categorical variables will be compared by Fisher's exact test. Continuous variables will be compared by Student's *t*-test or the Wilcoxon*-*Mann*-*Whitney test, as appropriate. Statistical analysis will be carried out using the R studio software. A *p*-value <0.05 will be considered statistically significant.

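### The exclusion for an ICU stay under 48 h cannot be known at randomisation, and it is not reconciled with the intention-to-treat analysis

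*Protocol article*

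**What the plan says.** In the protocol article, Table 2 (Study Population) lists inclusion and non-inclusion criteria and then, under a separate heading for exclusion criteria, one entry: "<48 h ICU Lenght of stay". Table 1 places ICU admission, enrolment and randomisation all at H0 (Day 0).

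The Randomization section states: "A second check for the inclusion, non-inclusion, and exclusion criteria is required before continuing with the randomization".

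Under Endpoints, "The primary endpoint is the number of patients with a lactate clearance over 10% between H0 and H2". The last item in the list of secondary endpoints reads "ICU length of stay, hospital length of stay, and 28-day mortality. Patients' follow-up is 28 days after enrolment".

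On analysis sets, the Data Analysis Plan says "The data will be analyzed by intention to treat and per protocol" and does not mention short-stay patients. The Sample Size Calculation goes from 82 to 90 per arm with the words "After taking into account the risk of missing data and patients lost to follow-up (10% of incomplete data", and does not mention exclusions.

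The Discussion gives a safety reason for a different exclusion, the one for haemodynamic deterioration. It gives no reason for the 48 h criterion.

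**The concern.** A stay of less than 48 h is something that happens to a patient after allocation. The obvious ways to have one are death in the ICU, discharge after quick recovery, or transfer. The first two may depend on the resuscitation strategy under test, and ICU stay and mortality are themselves endpoints of the trial.

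If the criterion is applied to the analysis, three things are at stake:

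- **Primary endpoint.** It is complete at 2 h, so patients with a known result could be discarded because of what happened over the next 46 h. The groups compared would no longer be those that were randomised.
- **Secondary endpoints.** ICU deaths before 48 h would be missing from 28-day mortality, and ICU length of stay would have no values below 48 h.
- **Sample size.** The 10% allowance is described as covering missing data and loss to follow-up. Exclusions would come out of the same 90 per arm.

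**Working it through.** **1. Can the criterion be applied as the article requires?**

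- Randomisation is at H0 (Table 1). The stay becomes known at the end of the ICU stay or at 48 h, whichever comes first.
- The Randomization section requires the exclusion criteria to be checked before randomisation. An actual stay cannot be checked then.
- The entry cannot sensibly mean time already spent in the ICU, because that would bar every patient enrolled at admission.
- An actual stay can therefore be acted on only after randomisation. Removing randomised patients on that basis is incompatible with analysing them as randomised.

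**2. The plan's sample size**

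Inputs from the Sample Size Calculation: control rate 60% (upper end of the stated 50–60%), algorithm rate 80%, two-sided alpha 5%, power 80%. Mean rate 0.70.

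n = [1.960·√(2·0.70·0.30) + 0.842·√(0.60·0.40 + 0.80·0.20)]² / 0.20²
= (1.270 + 0.532)² / 0.04 = 3.249 / 0.04 = 81.2, so 82 per arm.

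This reproduces the stated 82. With the allowance, 82/0.90 gives 92 and 82 × 1.10 gives 91; the stated 90 is within two patients. The sample size is not the error here.

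**3. Power of the planned test without the exclusion**

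Fisher's exact test, 60% vs 80%, exact calculation:

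- 90 per arm: 80.2%
- 82 per arm: 75.9%
- 81 per arm (90 × 0.90): 75.3%

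**4. Power if short-stay patients are removed**

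The documents give no rate of stays under 48 h, so the removal rates are assumptions, applied equally in both arms.

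*20% of non-responders and 10% of responders removed:*

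- Control: 54 × 0.90 + 36 × 0.80 = 48.6 + 28.8 = 77.4 remain; observed rate 48.6/77.4 = 62.8%.
- Algorithm: 72 × 0.90 + 18 × 0.80 = 64.8 + 14.4 = 79.2 remain; observed rate 64.8/79.2 = 81.8%.
- Fisher power (77 and 79): 73.7%.

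*30% and 20% removed:*

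- Control: 43.2 + 25.2 = 68.4 remain; observed rate 63.2%.
- Algorithm: 57.6 + 12.6 = 70.2 remain; observed rate 82.1%.
- Fisher power (68 and 70): 67.7%.

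With equal removal in both arms the difference moves only from 20 to about 19 points. The loss here is mainly one of numbers.

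**5. Bias if removal differs between arms**

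Take no true effect, 60% in both arms, with removal in one arm only (rates again assumed). Write e1 and e0 for the fractions of responders and non-responders removed. Observed rate = 0.60(1−e1) / [0.60(1−e1) + 0.40(1−e0)].

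- e1 = 5%, e0 = 25% (early deaths dominate): 0.57/0.87 = 65.5%, a shift of +5.5 points.
- e1 = 25%, e0 = 5% (early recoveries dominate): 0.45/0.83 = 54.2%, a shift of −5.8 points.

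In either case the two-sided Fisher test rejects in about 10% of trials, against less than 4% with no exclusion. A larger sample would not remove this.

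**The case against.** A reader might infer that the trial will drop all early deaths and early recoveries and that its intention-to-treat analysis is already broken. The article does not support that. It nowhere says these patients leave the intention-to-treat set. It names both analyses, and one reading is that the 48 h rule defines only the per-protocol set or the protocol follow-up. Detailed analysis-set definitions are commonly left to a full protocol or SAP, which are not shown. This limits how firmly the consequences can be stated. It does not remove the point, because the criterion itself is stated, and as worded it conflicts with two other sections.

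A second reading is that an expected stay under 48 h is meant, judged at enrolment. The pre-randomisation check leaves some room for this. Against it, Table 2 does not say expected, and it separates this entry from the non-inclusion criteria. If that is the intention, the wording still has to change.

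The size is also open to challenge, and here most of the objection stands:

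- The removal rates are assumed, and how 2-h clearance relates to a short stay is conjecture. The direction of any bias cannot be derived from the documents.
- The fairer baseline is the plan's own allowance. At 82 per arm Fisher power is already about 76%, so the milder scenario costs about 2 points beyond that, unless missing data come on top of the exclusions.
- The shortfall from 80% to about 76% comes from pairing Fisher's test with a sample size that matches a pooled z-test, which is a separate matter.
- The statement that "no provision is made for patient replacement" concerns patients for whom the study is discontinued. It should not be read as a rule about the 48 h exclusion.

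Finally, H48 lactate cannot be measured in the ICU on someone who has left it. That affects the later secondary time points and does not justify removing a patient from the H2 endpoint or from mortality.

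**Conclusion.** The point holds as a contradiction within the article. An exclusion on actual ICU stay under 48 h cannot be checked before randomisation as required. Taken literally it selects on a post-randomisation outcome, and it conflicts with the stated intention-to-treat analysis. What happens to these patients in the analysis is not stated and must be.

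If they are removed, the primary comparison can be biased in either direction (about 5 to 6 points under the assumed one-arm losses). Early ICU deaths would be lost from 28-day mortality. Fisher power would be about 74% or 68% in the two illustrative scenarios, against 80% with all 90 per arm and about 76% at 82 per arm. All these figures rest on 60% vs 80% (60% in both arms for the bias case) and on exclusion rates that the documents do not give. If every randomised patient stays in the intention-to-treat analysis, none of this loss arises and only the wording needs correcting.

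**What to change.** - Delete the 48 h entry from Table 2, or restate it using only information known before randomisation.
- State that every randomised patient is analysed by intention to treat for H2 clearance and 28-day mortality, whatever the ICU stay.
- Confine any 48 h restriction to a per-protocol or sensitivity analysis, and label it so.
- For lactate from H12 to H48, treat earlier death or discharge as an intercurrent event with a stated strategy, not as an exclusion.

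The cost is one line in Table 2, matching SAP wording, and vital-status follow-up to day 28 for patients with short stays. No extra patients are needed.

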### Study Intervention

Care of the patients is standardized and follows international guidelines and in-hospital protocols (1, 16–19). Preload dependence is assessed using the passive leg raising maneuver and/or the fluid challenge maneuver. Preload dependence is treated with a fluid bolus (250–500 ml) of Ringer Lactate for over 15 min. Cardiac output is optimized first by optimizing preload, and in the absence of preload dependency, by intravenous administration of dobutamine to obtain a cardiac index (CI) >2.5 L min^−1^ m^−2^. Cardiogenic failure is treated by intravenous administration of dobutamine (2.5–10 μg kg^−1^ min^−1^). Cardiac output can be measured by using echocardiography (Affinity or Epiq Philips™), pulmonary artery catheter, trans-pulmonary thermodilution (PiCCO device, Maquet™), or by Pressure Recording Analytical Method (Mostcare, Vygon™, France) (15). Vasoplegic syndrome is treated by intravenous infusion of norepinephrine (0.01 to 2 μg kg^−1^ min^−1^). Additional use of vasopressin if the norepinephrine dose is over 0.2 μg kg^−1^ min^−1^ is permitted. In accordance with the guidelines, we use a threshold of Hb <70 g/L for transfusion, in the absence of coronary artery disease. In patients with coronary artery disease, the threshold for transfusion is Hb <100 g/L. The mechanical ventilation parameters are adjusted on the basis of arterial blood analysis results. Baseline ventilator settings are as follows: respiratory rate of 10–18 breaths/min, tidal volume of 4–8 ml/kg, positive end-expiratory pressure of 5–10 cmH_2_O, a fraction of inspired oxygen of 0.25–1, targeting proper PaO_2_ of 100–120 mmHg, and PaCO_2_ of 35–45 mmHg. None of the non-hemodynamic therapies will be discontinued, and the drug dose regimen will not be modified. These therapeutic strategies do not differ in the two study groups. In the algorithm group, pCO_2_ is measured by central blood gas analysis.

The study intervention consists of treatment of hyperlactatemia following either an algorithm based on the pCO_2_ gap/P(a–v)O_2_ ratio and pCO_2_ gap or usual clinical practice based on macrohemodynamics, respecting randomization. If hemodynamic deterioration occurs despite hemodynamic optimization, a patient is excluded from the study and is treated following usual clinical protocols.

The algorithm is shown in Figure 1. Usual clinical practice is shown in Figure 2.

